## Abstract

**Background:**

A multitude of different diseases—benign and malign—can require surgery of the liver. The liver is an especially challenging organ for resection planning due to its unique and interindividually variable anatomy. This demands a high amount of mental imagination from the surgeon in order to plan accordingly - a skill, which takes years of training to acquire and which is difficult to teach. Since the volume of the functional remnant liver is of great importance, parenchyma sparing resections are favoured. 3D reconstructions of computed tomography imaging enable a more precise understanding of anatomy and facilitate resection planning. The modality of presentation of these 3D models ranges from 2D monitors to 3D prints and virtual reality applications.

**Methods:**

The presented trial compares three different modes of demonstration of a 3D reconstruction of CT scans of the liver, which are 3D print, a demonstration on a regular computer screen or using a head-mounted virtual reality headset, with the current gold standard of viewing the CT scan on a computer screen. The group size was calculated with *n*=25 each. Patients with major liver resections in a laparoscopic or open fashion are eligible for inclusion. Main endpoint is the comparison of the quotient between planned resection volume and actual resection volume between these groups. Secondary endpoints include usability for the surgical team as well as patient specifics and perioperative outcome measures and teaching issues.

**Discussion:**

The described study will give insight in systematic planning of liver resections and the comparison of different demonstration modalities of 3D reconstruction of preoperative CT scans and the preference of technology. Especially teaching of these demanding operations is underrepresented in prior investigations.

**Trial registration:**

Prospective trials registration at the German Clinical Trials register with the registration number DRKS00027865. Registration Date: January 24, 2022.

**Supplementary Information:**

The online version contains supplementary material available at 10.1186/s13063-022-06347-0.

## Administrative information

Note: the numbers in curly brackets in this protocol refer to SPIRIT checklist item numbers. The order of the items has been modified to group similar items (see http://www.equator-network.org/reporting-guidelines/spirit-2013-statement-defining-standard-protocol-items-for-clinical-trials/).

## Introduction

### Background and rationale {6a}

Every year, about 80,000 patients are treated in German hospitals for primary hepatic malignancies or metastases of the liver. Approximately 30,000 of those undergo liver resection each year [1]. Resectability of a liver tumour is determined by technical and functional aspects: the tumour needs to be removed with a sufficient resection margin while maintaining a future liver remnant of sufficient size, which is estimated to be 25% of the staring volume [2]. Since liver function cannot be artificially replaced the risk of postoperative liver failure after liver resection is estimated to be 6–23% depending on the extent of resection [3]. Liver surgery is challenging and requires accurate planning due to the liver’s unique anatomical structure as a parenchymatous organ and its division into eight anatomical segments. Each liver segment is supplied with blood by an artery and a portal vein and drained by the hepatic veins as well as bile being drained by the bile duct [4]. The anatomical division into liver segments is highly variable from patient to patient and not visible on the liver surface [5]. Due to this high interpatient variability liver resections need to be individualized and resection planning prior to the operation date is vital. Usually, this planning step is conducted by the surgeon using a contrast-enhanced CT scan or MRI of the Liver and its blood vessels. The two-dimensional pictures need to be transformed into a three-dimensional model threaded with blood vessels and bile ducts by the surgeons power of imagination. This skill set is integral to hepatobiliary surgery and demands years of training [6]. It is a skill, which is not only demanding to learn but also challenging to teach. In order to facilitate easier planning and teaching, computer-based procedures to obtain a three-dimensional model of the liver using a pre-existing CT scan have been developed [7, 8]. This is an individualized process and thus takes the interpatient anatomical variabilities into account [9]. These 3D models allow for planning of the operation and calculation of the resection volume, usually using an interactive PDF displayed on a conventional two-dimensional computer screen [10]. The virtual 3D model of the liver can be rotated and zoomed in as needed in the program. A second option of displaying this three-dimensional data set is a 3D print, in which the liver tissue is displayed in transparent plastic enabling blood vessels, bile duct, tumour and cysts to be visible from the outside [11, 12]. The surgeon can pick up the model and rotate it in her or his hands and plan the resection accordingly. A third modality of displaying a 3D reconstruction of the liver is a virtual reality (VR) application using a head-mounted display [13]. The surgeon can view the model and rotate and zoom as needed. Furthermore, transparency of different structures can be increased and decreased to allow for better visibility. All of the three aforementioned demonstration modes of a 3D reconstruction of the liver alleviate the surgeon of the task of reconstructing the CT scan mentally in ones’ head [14]. In addition all three modes facilitate the surgeon to share her or his thoughts with residents or students more easily enabling them to teach and supervise resection planning [15].

A previously conducted preclinical study compared the three modalities and found an improved visualization in 3D VR with head-mounted displays and 3D print [16]. In the current study, the clinical application of the described systems in a prospective randomized controlled trial is the focal point.

The interventions are compared to the current standard of viewing the CT scan on a regular computer screen. Therefore there is no placebo or sham group in action, which could potentially harm a patient. The regular CT scans are available to the surgical team at all times, during planning as well as during operation. The interventions act as supplement to the gold standard and have the potential to not only aid the surgeon but also the teaching of residents and students. The trial is expected to show, which demonstration modality of 3D models is helpful for liver resection planning and which demonstration mode facilitates the highest usability and best outcome. Generating a 3D model of the liver is a time-consuming task [7] and costs of 3D prints and VR head-mounted displays and personal computers capable of displaying VR content make economical deliberations necessary and obvious. The results of this study may help in the decision process, whether these techniques should and can be applied on a regular basis or only for well-chosen cases.

### Objectives {7}

The objective of the trial is to compare the three demonstration modes of a 3D reconstruction of the liver, being 3D PDF, 3D print and 3D VR using a head-mounted display, to the current gold standard of a 2D CT scan displayed by a regular computer screen. The main end-point is the comparison of planned resection volume (RLV1) and actual resection volume (RLV2) measured by water displacement volumetry ((RLV2-RLV1)/RLV1). Furthermore, patients’ characteristics as well as intraoperative outcome and postoperative morbidity and mortality will be assessed to ensure comparability of study groups. The surgical team will be presented a questionnaire to usability and handling of the demonstration modes.

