## Interventions

### Explanation for the choice of comparators {6b}

Resection volume in liver surgery is a critical parameter correlating both to liver failure as well as postoperative morbidity. The presented trial aims to compare planned resection volume and actual resection volume throughout the aforementioned demonstrations modes to see which mode enables the most accurate prediction of resection volume. Furthermore, usability scores and handling of the different demonstration modes will be compared to determine, if one mode is preferable over the others. Patients’ characteristics as well as intraoperative outcome and postoperative morbidity and mortality are recorded for descriptive statistics and to unveil any imbalances of the study group. To compare patients’ general condition, the Charleson Comorbidity Index [17] is used; to assess postoperative complications, Dindo-Clavien Score and the comprehensive compication index are used.  (DOI: 10.1097/SLA.0000000000002902 [18]).

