### Outcomes {12}

Primary outcome is the quotient of planned resection volume (RLV1) and actual resection volume (RLV2) calculated as (RLV2-RLV1)/RLV1. The resection volume will be measured in millilitres; planned resection volume will be measured using one of the four demonstration modes and volumetry no late than the day before surgery. Actual resection volume will be measured the day of surgery. This parameter is critical to determine how accurate the predicted resection volume is between the different groups.

Secondary outcome consists of usability and subjective task load using SUS and the NASA TLX. A system is less likely to be used, if it is complicated or the controls are hard to remember or challenging to conduct. Thus these scores will show if implementation into daily clinical use is feasible for the different demonstration modes. The described systems are being tested in order to simplify liver resection planning and teaching, thus these measures are critical to determine usability and likelihood of daily use.

Furthermore, patients’ characteristics as well as intraoperative outcome (i.e. resection margin, blood loss, duration of surgery), pathological findings and postoperative morbidity and mortality are assessed in order to describe the study collective properly. Since liver resections can vary greatly in extent even in the chosen group of major resections, it is important to put patients’ characteristics and intraoperative and postoperative measures into perspective with the planned and actual surgical procedure.

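### Intraoperative and postoperative outcomes are given the job of checking group comparability, which measures taken after the intervention cannot do, and their endpoint status differs between sections

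*Protocol article*

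**What the plan says.** The protocol article gives the same group of measures several roles.

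- Objectives {7}: besides patient characteristics, intraoperative outcome and "postoperative morbidity and mortality will be assessed to ensure comparability of study groups".
- Explanation for the choice of comparators {6b}: characteristics, intraoperative outcome, morbidity and "mortality are recorded for descriptive statistics and to unveil any imbalances of the study group".
- Abstract, Methods: "Secondary endpoints include usability for the surgical team as well as patient specifics and perioperative outcome measures and teaching issues".
- Outcomes {12}: "Secondary outcome consists of usability and subjective task load using SUS and the NASA TLX". Resection margin, blood loss, duration of surgery and pathological findings come in a separate paragraph, where they and "postoperative morbidity and mortality are assessed in order to describe the study collective properly".
- Background and rationale {6a}: the trial is expected to show "which demonstration mode facilitates the highest usability and best outcome".

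Statistical methods {20a} treats patient characteristics and perioperative and postoperative outcomes together. It summarises them in the same way and compares groups by t-test, or by chi-square test for dichotomous variables.

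**The concern.** Comparability of randomised arms is a statement about the patients before the intervention acts. Blood loss, operating time, complications and death come afterwards and can be changed by it. Using them as a balance check reverses their meaning: if one planning mode led to less blood loss or fewer complications, the stated purpose would label that an imbalance between groups and not a possible effect.

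The conflict over endpoint status adds a second difficulty. A reader cannot tell from the article whether these measures are secondary endpoints, background description or a check on randomisation. The same observed difference could later be reported in any of the three ways. At stake is the interpretation of the secondary clinical results.

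**Working it through.** No arithmetic applies. The plan attaches no figure to this point, and the sample size (23 per group, raised to 25) concerns the primary outcome. The check compares timing and stated roles.

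**Step 1: when each item is recorded** (Participant timeline {13}, Table 1). Intervention description {11a} has the allocated display shown to the surgeon by the day before surgery at the latest.

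| Item | Recorded | Relative to randomisation and planning display | Can show baseline balance? |
|---|---|---|---|
| Patient characteristics | Enrolment | Before | Yes |
| Intraoperative specifics ({12} names margin, blood loss, duration) | Day of surgery | After | No |
| 30-day morbidity and mortality | POD 30 | After | No |
| 90-day mortality | POD 90 | After | No |

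**Step 2: could the planning mode affect the later items?** The protocol's own text leaves this open. The 3D print and 3D PDF are also available in the operating room to their groups ({11b}), and {6b} links resection volume to liver failure and postoperative morbidity. An effect is possible, so a difference in these items cannot be assigned to imbalance in advance.

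**Step 3: are the stated roles compatible?**

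- Abstract against Objectives and {6b}: for an endpoint, a between-arm difference is a possible effect. For a balance check, the same difference is evidence that the groups differ. One measure cannot carry both meanings.
- Abstract against Outcomes {12}: the Abstract counts perioperative measures as secondary endpoints. Outcomes {12} limits the secondary outcome to SUS and NASA TLX and uses the rest to describe the patients.
- The Abstract also lists patient-specific data as an endpoint. Table 1 records patient characteristics at enrolment, so these are baseline data and the right material for judging comparability. In effect the two kinds of variable have changed places.

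**Step 4: what would the analysis do?** Under {20a} the groups are compared on these variables, so a difference would be displayed and tested. The error is confined to the reason given for looking at it.

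**The case against.** The strongest reply is that this is a matter of labels in an exploratory trial (Trial design {8}) sized for volume accuracy. Much of that stands.

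- A reader might infer that the primary comparison is biased through adjustment for, or exclusion on, these outcomes. The article does not support this. The primary outcome is analysed by a Wilcoxon test with no covariates mentioned ({20a}), and {20b} plans no additional analyses. The analysis with and without outliers raised in the Discussion turns on very large tumours needing extensive resection, and not on a postoperative result.
- A reader might count Outcomes {12} as a third place that uses these measures to check comparability. It does not: it describes the patients and relates the measures to the planned and actual procedure. The comparability role is stated outright in Objectives {7}. In {6b} it stands second to description.
- A reader might infer that a real effect would be explained away. No section says so. The stated purpose points that way, but the result would be visible.
- A reader might try to count the false imbalances that baseline significance tests would produce. That is a separate matter, and the article fixes neither the contrasts nor the significance level for these variables, nor their number.
- The Abstract's perioperative measures plainly include blood loss. Whether they include 30-day morbidity and 90-day mortality is arguable, since {20a} names perioperative and postoperative outcomes separately. The best-outcome phrase in {6a} is background wording and may mean the primary outcome.

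The article also expects no added risk ({30}) and no impact on patient safety ({21b}). That expectation does not make measures taken after the intervention into baseline variables.

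**Conclusion.** Wrong as written, minor in severity. Objectives {7} and {6b} assign outcomes that follow the intervention to a check of comparability or imbalance, which they cannot perform. That role conflicts with the Abstract, and the Abstract conflicts with Outcomes {12}. This is a wrong stated purpose and an internal contradiction, not detail that could be left to an analysis plan.

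The effect is limited to what a between-arm difference in blood loss, morbidity or the other listed measures is taken to mean. It has no numerical size in the documents. The conclusion rests only on the order of events in Table 1 and {11a} and on the wording of the sections set out above; it does not require that the planning mode actually changes any clinical outcome.

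**What to change.** 1. In Objectives {7} and {6b}, restrict the judgement of comparability to patient characteristics recorded before randomisation, for example age and the Charlson index, tabulated by arm. Items from the preoperative planning questionnaire should not be used for this, because Table 1 places that questionnaire after allocation.
2. In the Abstract and Outcomes {12}, list resection margin, blood loss, duration of surgery, 30-day morbidity and 30- and 90-day mortality consistently as exploratory secondary outcomes. Report them by randomised arm as differences with 95% confidence intervals.
3. Remove the patient-specific data from the endpoints in the Abstract.
4. State that the intraoperative and postoperative outcomes are not used to judge baseline balance.

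The cost is a change of wording in four places plus one added sentence. The outcomes listed are already named for collection in Outcomes {12} and Table 1, and the sample size and primary analysis are unaffected.

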### Trial design {8}

The study is designed as an exploratory prospective randomized trial with even allocation into all four study groups.

## Methods: participants, interventions, and outcomes

### Study setting {9}

The trial is planned as a monocentric study in the University hospital Mainz, Germany in the Department for General, Visceral and Transplant surgery. The department is among others specialized in hepatobiliary surgery with a case load of more than 300 liver resections each year.

### Eligibility criteria {10}

Inclusion criteriaElective primary conventional or laparoscopic liver resectionAnatomical or atypical liver resectionMajor liver resection (>3 segments)Age >18 yearsAvailability of a three-phase contrast-enhanced CT scanWritten consent

Exclusion criteriaMinor liver resectionRecurrent liver resectionMulti-visceral resection planned (i.e. simultaneous colon resection)Cirrhosis of the liver Child B or Child C

### Who will take informed consent? {26a}

The patients will be screened for eligibility in the outpatient clinic, where all patients of the department are presented for evaluation of resectability and preparation for operation. The researchers of the study team are trained physicians with experience in hepatobiliary surgery and will conduct the screening as well as the informed consent. Eligible patients will be offered the opportunity to participate and included or excluded based on their decision.

### Additional consent provisions for collection and use of participant data and biological specimens {26b}

The data collected include patient specifics as well as intraoperative and postoperative outcome data, patients are asked for written consent to recording and publishing these data anonymously. On the written consent form participants are informed, that they can withdraw from consent at any time. In case of withdrawal the data will not be used. There is no further data collection or obtainment of biological specimens in this study, hence this is not applicable.

## Interventions

### Explanation for the choice of comparators {6b}

Resection volume in liver surgery is a critical parameter correlating both to liver failure as well as postoperative morbidity. The presented trial aims to compare planned resection volume and actual resection volume throughout the aforementioned demonstrations modes to see which mode enables the most accurate prediction of resection volume. Furthermore, usability scores and handling of the different demonstration modes will be compared to determine, if one mode is preferable over the others. Patients’ characteristics as well as intraoperative outcome and postoperative morbidity and mortality are recorded for descriptive statistics and to unveil any imbalances of the study group. To compare patients’ general condition, the Charleson Comorbidity Index [17] is used; to assess postoperative complications, Dindo-Clavien Score and the comprehensive compication index are used.  (DOI: 10.1097/SLA.0000000000002902 [18]).

### Intervention description {11a}

After written consent, the patients are randomized into one of four groups using an envelope system. Randomization is not conducted by the researchers but by an impartial study nurse. Reconstruction of the preoperative CT scan into a 3D data set is performed by the researchers of the study group in the program Synapse 3D (Fujifilm Europe GmbH, Düsseldorf). In case of randomization into the 3D print group, the data set is anonymized and STL files are sent to a cooperating company (Cella Medical Solutions, Murcia, Spain) for printing. According to randomization, the 3D data set is then displayed to the surgeon assigned to the case not later than the day before surgery for resection planning. The surgeon is assisted by a member of the study group in terms of technical support and calculation of the planned resection volume (RLV1). At the end of surgery, the actual resection volume (RLV2) is determined by water displacement volumetry. A questionnaire about usability and subjective task load using the System Usability Scale (SUS) [19] and NASA Task Load Index (TLX) [20] is presented to the surgeons after operation. The data will be collected in a local database, to which only researchers of the study group have access. Data will be stored for 10 years according to the requirements of the local ethics committee.

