## Assignment of interventions: blinding

### Who will be blinded {17a}

There is no blinding planned for this specific trial.

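### As the steps are ordered, the 3D reconstruction follows randomisation and is made by unmasked study researchers, so any arm-related difference in the model would be read as a display effect, chiefly among PDF, print and VR

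*Protocol article*

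**What the plan says.** The Intervention description {11a} of the protocol article gives the steps in sequence. It begins: "After written consent, the patients are randomized into one of four groups using an envelope system". It continues: "Reconstruction of the preoperative CT scan into a 3D data set is performed by the researchers of the study group", using one named program, Synapse 3D. Next comes a step that depends on the arm: "In case of randomization into the 3D print group, the data set is anonymized and STL files are sent to a cooperating company". Then: "According to randomization, the 3D data set is then displayed to the surgeon assigned to the case not later than the day before surgery". A study group member helps the surgeon to compute the planned volume, RLV1.

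Table 1 (Participant timeline {13}) places allocation at time 0 and both the 3D modes and the planned volume in the later +2 week column. It has no row for the reconstruction. Under Who will be blinded {17a}: "There is no blinding planned for this specific trial".

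The endpoint is defined under Outcomes {12}: "Primary outcome is the quotient of planned resection volume (RLV1) and actual resection volume (RLV2) calculated as (RLV2-RLV1)/RLV1". The Objectives {7} set out to "compare the three demonstration modes of a 3D reconstruction of the liver", with the CT scan on a screen as the reference. The section on the choice of comparators {6b} adds that the trial should reveal which mode predicts resection volume most accurately.

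**The concern.** Reading an accuracy difference as a property of the display assumes that what is displayed does not depend on the arm. Randomisation makes the patients comparable. It does not protect a step that people carry out afterwards and that may be influenced by knowing the arm. Segmenting a liver is manual work, and the Background {6a} calls building such a model time-consuming, so effort can vary from case to case.

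RLV1 appears in both the numerator and the denominator of the primary quotient. If segmentation differed between the PDF, print and VR arms, the comparison would mix model and display, and no later analysis could separate them.

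The safeguards in the article do not cover this step. The envelopes and the independent nurse protect the allocation. The second-researcher check under Data management {19} concerns data entries.

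**Working it through.** No stated figure has to be reproduced: the point concerns the order of steps and masking, and the sample size of 23 raised to 25 per group does not depend on it. The arithmetic only shows how large a drift would have to be to matter.

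**Inputs**
- SD of the quotient: 20% in the control group and 10% in each 3D group (Sample size {14}), read here as between-patient SDs.
- 25 patients per group and a local two-sided level of 0.017 (Sample size {14}).
- Relative change e in RLV1 due to segmentation: **an assumption**, since the documents give none. Shown for 2%, 5% and 10%.
- True quotient of 0 (RLV2 = RLV1), and a segmentation change that passes fully into RLV1: also assumptions.

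**Shift in the quotient.** If RLV1 becomes RLV1 × (1 + e) and RLV2 is unchanged, the quotient moves from 0 to 1/(1 + e) − 1. For e = 5%: 1/1.05 − 1 = −0.0476, or −4.8 points.

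**Standard errors**
- Two 3D arms: sqrt(10²/25 + 10²/25) = sqrt(8) = 2.83 points.
- 3D against CT: sqrt(20²/25 + 10²/25) = sqrt(20) = 4.47 points.

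| Assumed e | Shift (points) | In SEs, 3D v 3D | In SEs, 3D v CT |
|---|---|---|---|
| 2% | −1.96 | 0.69 | 0.44 |
| 5% | −4.76 | 1.68 | 1.06 |
| 10% | −9.09 | 3.21 | 2.03 |

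**Chance of a false display effect.** Suppose the display has no effect and one arm's mean quotient is shifted by an assumed b points. For a two-sided t test at 0.017 with 48 degrees of freedom and noncentrality b/SE, the chance of a significant result in the direction of the shift is:

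| Assumed shift b (points) | 3D v 3D | 3D v CT |
|---|---|---|
| 2.5 | 6% | 3% |
| 5 | 25% | 10% |
| 7.5 | 57% | 22% |
| 10 | 85% | 41% |

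The article plans a Wilcoxon test for the primary outcome, so these t-test figures are only a yardstick.

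**The case against.** Several points can fairly be made on the other side.

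- **Timing and knowledge of the arm are inferred.** No sentence dates the reconstruction; its place after allocation comes from the order of the text. The sentence on print files is passive and describes a step after the data set exists, so it does not show that the person segmenting knew the arm. The absence of blinding permits that knowledge but does not prove it. This stands, and the point is therefore worded as a lack of protection.
- **The text suggests one common process.** The reconstruction sentence carries no condition on the arm; only the display follows allocation. A reader might infer that more care will go into models to be printed or shown in VR. Nothing in the documents supports that.
- **Against CT, the model belongs to the intervention.** A reader might also infer that every 3D-versus-CT comparison is confounded. That goes too far: the 3D model is a supplement that the control arm is not shown, and the article does not make clear whether or how control scans are reconstructed for RLV1. The sample size assumptions suggest that the 3D-versus-control contrasts are the powered ones, and the trial is called exploratory. This narrows the concern to the comparisons among 3D modes.
- **The illustration assumes a one-directional shift.** Unequal care might instead change the spread, and a segmentation change need not pass one-for-one into RLV1, which also depends on the resection the surgeon plans. This stands: the figures show what could matter, not what will happen.

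That an article condenses its protocol is a weak reply here. The section on data access {31c} says the full protocol is accessible in the manuscript, and the point concerns a sequence that the article does state.

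**Conclusion.** The concern holds as a conditional risk of bias. As the article orders the steps, and with no masking planned, nothing keeps the reconstruction independent of the allocated display mode. An arm-related difference in segmentation would be taken for a display effect, chiefly in PDF v print v VR.

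The documents do not establish that such drift occurs, nor its direction. Under the assumed 5% change in RLV1, the shift of −4.8 points is about 1.7 SE between two 3D arms and about 1.1 SE against CT. This rests on the planned SDs, 25 per arm, a true quotient of 0 and full transfer of the change into RLV1. The change is worth making because it is cheap and because analysis cannot remove the bias afterwards.

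**What to change.** In the Intervention description {11a}, state that the Synapse 3D data set is completed and locked before the envelope is drawn, or before the arm is released to the person segmenting. Use that one locked data set for display, print and volumetry, and log any later edit with its reason.

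Read literally, the article already reconstructs every patient's scan, so this only reorders a step and adds a lock date and time to the CRF. If control scans are in fact not reconstructed, locking before allocation would add about 25 reconstructions. To avoid that, the nurse can first release only whether the patient is in a 3D arm or the control arm, and release the 3D mode after the lock. That still protects the comparisons among 3D modes.

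Sample size and patient care are unchanged. The change belongs before recruitment, which had not begun at this version (Trial status). It leaves the unmasked help with calculating RLV1 in place, which should be acknowledged as a limitation.
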